### **Statistical analysis**

Descriptive statistics will be conducted to compare the baseline status between the two groups.

Data will be analyzed on an intention-to-treat (ITT) basis. In accordance with the ITT principle, all patients will be included in the analysis, independently of the groups to which they are randomly assigned and regardless of whether they complete the treatment or not. Participants who breach the protocol (taking cessation medication or received other cessation treatment) will be followed-up in their original group and classified according to their smoking status consistent with other participants.

The Russell Standard (RS) will be used in this study. All randomized subjects will be included in the denominator for calculating abstinence rates with the exception of unavoidable loss to follow-up (died or moved to an untraceable address). Those who decline to be involved in subsequent data collection will be counted as smokers. This type of analysis is considered the most conservative and is the standard for smoking cessation studies.

The primary and secondary abstinence outcomes will be analyzed by logistic regression of smoking status at each timepoint. The dependent variable is smoking

status (still smoking=0, abstinent=1). The independent variable is each intervention versus the control condition. Odds ratios (Or) will be used to measure the outcomes for the intervention groups compared to the control group, and 95% confidence intervals (CI) and P values will be reported to infer efficacy. In sensitivity analyses, each model will be further adjusted for baseline covariates: living area, age, education, smoking frequency and nicotine dependence at baseline.

All data will be analyzed using SPSS version 21.0. The level of bilateral significance for all statistical tests will be established at  $\alpha = 0.05$ .

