### **Secondary objectives**

1. To evaluate potential impact on health awareness and self-efficacy for smokers between the two kinds of interventions.

2. To identify whether certain patients are more likely to benefit from these interventions.

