### Primary and Secondary outcome

The primary outcome was the biochemically verified 6 month sustained abstinence rate, defined as the self-report of no smoking any cigarettes after the designated quit date, validated biochemically by an expired carbon monoxide level of less than 6 ppm at each follow-up point.

Secondary outcomes are comprised of two aspects:

1. biochemically verified sustained abstinence rate at 1 month, 3 months, 1-3 months and 3-6 months, biochemically verified 24-hour point prevalence of abstinence at each follow-up point, self-reported sustained abstinence rate and 24-hour point prevalence of abstinence at each follow-up point

2. the change in nicotine dependence measured by the Fagerstrom Test for Nicotine Dependence, the change in nicotine withdrawal symptoms measured by the Minnesota Nicotine Withdrawal Scale, and the change in the readings of expired carbon monoxide.

3. Smoking cessation related health behavior: stage of change, self-efficacy, threat appraisal, coping appraisal and protection motivation.

4. Utilization of the app: time application opened, time of utilization, function used and self-report preference.

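### The Statistical analysis section lets P values for 13 secondary abstinence outcomes, as well as the primary, carry an efficacy inference at a full two-sided 0.05

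*Protocol*

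**What the plan says.** Under Primary and Secondary outcome, the protocol fixes one primary endpoint: "The primary outcome was the biochemically verified 6 month sustained abstinence rate". The Sample size section is built on that endpoint alone (4% against 10%, 80% power, two-sided 0.05, 280 per group).

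The same outcome section lists three kinds of secondary abstinence outcome. The first is sustained abstinence with carbon monoxide confirmation over four periods: "biochemically verified sustained abstinence rate at 1 month, 3 months, 1-3 months and 3-6 months". The second is point prevalence over 24 hours, also confirmed by carbon monoxide, at every visit. The third repeats both measures on the participant's word alone: "self-reported sustained abstinence rate and 24-hour point prevalence of abstinence at each follow-up point".

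The Statistical analysis section puts them together with the primary: "The primary and secondary abstinence outcomes will be analyzed by logistic regression of smoking status at each timepoint". For these models it says that odds ratios will be given and that "95% confidence intervals (CI) and P values will be reported to infer efficacy". It closes by fixing one two-sided level, 0.05, for every test: "The level of bilateral significance for all statistical tests will be established at" that value. The section gives no order of testing and does not describe any abstinence outcome as supportive.

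**The concern.** Taken together, these sentences give 14 outcomes one model, one inferential purpose and one significance level. The primary is singled out where outcomes are defined and where the trial is sized, but not where inference is defined. A report that followed the text literally could cite a significant self-reported 1-month result as evidence of efficacy after the verified 6-month result had failed.

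At stake is the standard of evidence behind an efficacy statement. The design controls error for one demanding endpoint. The analysis wording opens 13 further routes to such a statement, six of them on self-report without carbon monoxide verification, and the trial was not sized for any of the 13.

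**Working it through.** **The plan's own figure.** With 4% and 10%, two-sided 0.05 and 80% power, the unpooled formula gives n = (1.960 + 0.842)² × (0.04×0.96 + 0.10×0.90) / 0.06² = 280 per group, as stated. The pooled version gives 283. This confirms that the sample size serves a single test of the primary at two-sided 0.05, with no allowance for other efficacy tests.

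**Counting the tests.** The Follow-up visit arrangement section sets visits at months 1, 3 and 6.

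| Abstinence outcome | Tests |
|---|---|
| Primary: verified sustained, 6 months | 1 |
| Verified sustained: 1 month, 3 months, 1-3 months, 3-6 months | 4 |
| Verified 24-hour point prevalence, three visits | 3 |
| Self-reported sustained, three visits | 3 |
| Self-reported 24-hour point prevalence, three visits | 3 |
| Total | 14 (13 secondary) |

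Table 2 also marks smoking status at month 2. If that counted as a follow-up point, there would be 16 or 17 tests. The figures below use 14.

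**Error rate with independent tests.** If all null hypotheses are true, the chance of at least one P < 0.05 in either direction is 1 − 0.95^14 = 0.512. The chance of at least one significant result favouring the intervention is 1 − 0.975^14 = 0.298. For a single test these are 0.05 and 0.025.

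**Allowing for correlation.** The outcomes overlap heavily, so independence is an upper reference and not a realistic case. The protocol gives no correlations. Assume 14 standard normal test statistics with a common correlation r, and a critical value of 1.96:

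| Assumed r | Any significant result | At least one favouring the intervention |
|---|---|---|
| 0 | 0.51 | 0.30 |
| 0.3 | 0.44 | 0.22 |
| 0.5 | 0.35 | 0.17 |
| 0.7 | 0.25 | 0.12 |
| 0.9 | 0.14 | 0.07 |

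The 13 secondary tests alone give almost the same either-direction values (0.49 at r = 0, 0.33 at r = 0.5, 0.14 at r = 0.9). The secondaries therefore account for nearly all of the excess.

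**Cross-check at participant level.** Null trials were simulated with 336 per arm (672 / 2), nested abstinence outcomes and Wald tests of the log odds ratio. Five sets of assumed rates were used, with self-reported sustained abstinence of 15% to 30% at month 1 falling to 6% to 12% at month 6. At least one of the 14 tests was significant, in either direction, in 24% to 34% of trials. The mean correlation between outcomes was 0.36 to 0.63, which agrees with the middle of the table.

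**The case against.** The case on the other side has four parts, and most of it stands.

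1. A hierarchy does exist. One primary is named, everything else is labelled secondary, and only the primary sizes the trial. The primary conclusion keeps its nominal 5%. This stands; what is missing is a distinct role for the primary in the inference wording.

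2. The protocol never promises 5% across the family. Its 0.05 is a per-test level, and the sentence about inferring efficacy reports results model by model. It is not a rule that any one significant test makes the trial a success. This also stands: the wording permits such a claim but does not direct it.

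3. A reader might infer that the trial has about a one-in-three chance of a false efficacy claim. The document does not support that. The 35% rests on an assumed correlation of 0.5 and counts results in both directions, including those favouring the control messages. For claims favouring the tailored messages, the figure under the same assumption is about 17%. A reader might also add the secondary objective "To identify whether certain patients are more likely to benefit from these interventions" to the count, but the protocol specifies no subgroup test, so there is nothing to count.

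4. Multiplicity rules for secondary outcomes are commonly left to the statistical analysis plan, which may exist and is not at hand. If the protocol were merely silent, this would dispose of the point. It is not silent: it assigns an efficacy purpose and a full 0.05 to the secondary abstinence outcomes. An analysis plan that confined efficacy to the primary would be narrowing the protocol's text, not filling a gap in it.

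**Conclusion.** The point holds as a fault in what the Statistical analysis section states. It gives 13 secondary abstinence outcomes the same inferential role and significance level as the primary, which does not fit a design that names and powers one endpoint. The validity of the primary test is not in question.

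If any one of the 14 tests were taken to show efficacy, the false-positive rate favouring the intervention would be about 7% to 30%, or 17% at r = 0.5, against 2.5% for a single test. In either direction it would be 14% to 51%, or 35% at r = 0.5, against 5%. These figures assume no true effect on any outcome, a common correlation between 0 and 0.9 that the protocol does not supply, and follow-up points at months 1, 3 and 6. The exact size is uncertain, but every value in the range exceeds the single-test level.

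**What to change.** In the Statistical analysis section, state that efficacy is inferred only from the test of verified 6-month sustained abstinence at two-sided 0.05. State that the other abstinence outcomes are supportive and will be reported with odds ratios and 95% confidence intervals.

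If the sponsor wants a confirmatory secondary claim, name one or two verified secondary outcomes and test them in a fixed sequence. Each would be tested at two-sided 0.05, and only if the primary and any preceding test are significant.

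The cost is one or two sentences. No patients or data are added, and the primary alpha, power and sample size do not change. The downside is that a significant secondary result could no longer be presented as evidence of efficacy when the primary is not significant.

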### **Randomization**

An independent statistician, [name] [name] from Guanghua School of Management, Peking University, will oversee the randomization but will not be involved in the treatment. After recruitment, participants were required to complete the baseline questionnaire and register through WeChat. With a randomized block design and the score of the Fagerström Test for Nicotine Dependence as a stratified factor, eligible participants were assigned to the intervention group or the control group. The WeChat system was also used to balance demographic characteristics. Randomization was fully computerized and automated with equal allocation. The researchers and participants were all blinded.

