### **Sample size**

The sample size calculation was based on the formula for a two-arm RCT. Based on earlier research, we estimated that biochemically verified continuous smoking abstinence at 6 months would be approximately 4% in the control group and 10% in the intervention groups. To achieve 80% power with a significance level of .05 (two sided), a sample size of 280 individuals was needed in each group. Assuming 20% attrition in the follow-up measurements, the total required sample size was 672.

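### The primary logistic model omits the Fagerström score on which randomisation is stratified; the test stays valid, but up to about 1.6 points of power are given away

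*Protocol*

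**What the plan says.** On allocation, the protocol (Randomization) reads: "With a randomized block design and the score of the Fagerström Test for Nicotine Dependence as a stratified factor", participants were assigned to one of two arms, with equal allocation. It adds: "The WeChat system was also used to balance demographic characteristics". It does not name those characteristics or the method of balancing.

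On analysis, the protocol (Statistical analysis) reads: "The primary and secondary abstinence outcomes will be analyzed by logistic regression of smoking status at each timepoint". The only predictor is treatment: "The independent variable is each intervention versus the control condition". Covariates follow as a second layer: "In sensitivity analyses, each model will be further adjusted for baseline covariates: living area, age, education, smoking frequency and nicotine dependence at baseline". Tests are two-sided at 0.05.

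The score is available for every randomised participant. The baseline questionnaire precedes allocation, and Table 2 lists nicotine dependence at baseline.

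**The concern.** When allocation is stratified on a factor, the usual practice is to carry that factor into the primary model, so that the analysis compares participants within the groups in which they were randomised. Here the protocol does this only in a model labelled as sensitivity. Because it states the main model outright, this is a choice already made and not a detail left for a statistical analysis plan.

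What is at stake is efficiency. If dependence predicts abstinence, stratification has already removed chance imbalance on it. A model without the score takes no credit for that, so its test can be a little conservative and a little less powerful than the same data allow.

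**Working it through.** **Inputs from the protocol (Sample size; Randomization; Statistical analysis).** Abstinence 4% control and 10% intervention; two-sided 0.05; 80% power; 280 per group; total 672 after 20% attrition; 1:1 allocation; blocks within Fagerström strata.

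**The plan's own figure.** Two proportions, unpooled variance:

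n = (1.960 + 0.842)² × (0.04 × 0.96 + 0.10 × 0.90) / 0.06² = 279.9, so 280 per group. This reproduces the stated number (pooled variance gives 283). The total follows as 560 × 1.20 = 672. The formula is unadjusted, so adding the score to the model does not alter it.

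**Planning odds ratio.** (0.10/0.90) / (0.04/0.96) = 2.67.

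**Expected events.** At 280 per group: 11.2 + 28.0 = 39. At 336 per group: 13.4 + 33.6 = 47. The analysed number probably lies between these, because most participants lost to follow-up stay in the denominator as smokers.

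**Simulation.** The protocol gives no strata cut-points, block size or prognostic strength, so these are assumptions: three strata holding 40%, 35% and 25% of participants; permuted blocks of 4 within stratum; odds of abstinence falling by a factor of 1 to 4 per step. Each setting used 560 participants and 4,000 trials. Every trial was analysed by Wald test with treatment alone and with treatment plus one linear stratum term. Arrows run from unadjusted to adjusted.

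| Odds ratio per step | Type I error, both arms 4% | Type I error, both arms 10% | Power, 4% vs 10% | Gain (points) | Conditional odds ratio |
|---|---|---|---|---|---|
| 1 | 0.044 → 0.044 | 0.043 → 0.043 | 0.803 → 0.803 | 0 | 2.67 |
| 1.5 | 0.035 → 0.037 | 0.051 → 0.052 | 0.799 → 0.801 | 0.2 | 2.68 |
| 2 | 0.041 → 0.043 | 0.040 → 0.043 | 0.796 → 0.801 | 0.5 | 2.71 |
| 3 | 0.039 → 0.041 | 0.044 → 0.050 | 0.811 → 0.821 | 1.05 | 2.75 |
| 4 | 0.039 → 0.043 | 0.044 → 0.053 | 0.807 → 0.823 | 1.6 | 2.79 |

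The Monte Carlo standard error is about 0.0035 on type I error. Both models were fitted to the same simulated trials, so the two columns in each pair can be compared directly. Some type I error below 0.05 appears in both models even when dependence has no effect; only the gap between the models can be put down to leaving out the score.

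**Further runs.** A second set (4,000 trials, odds ratios 1.5 to 3 per step) gave gains of 0.0 to 0.9 points at 672 participants and 0.2 to 1.4 at 560, with adjusted type I error of 0.044 to 0.050. A third (2,000 trials at 672) moved power from 0.873 to 0.875 at an odds ratio of 1.8 per step and from 0.865 to 0.873 at 2.5; type I error went from 0.048 to 0.049 and from 0.040 to 0.043. The only run that also adjusted for stage of change had 500 replicates. Its gains of 0.8 and 1.0 points lie inside its Monte Carlo error of 1.4 points, so it settles nothing about stage.

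**The case against.** The best defence is that nothing is broken. An unadjusted odds ratio is a legitimate primary estimand and matches a sample size built on two raw proportions. The model adjusted for dependence is already prespecified, so only the label of primary is in dispute. The gain is about a point. All of that stands, and it limits the point to efficiency.

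A reader might infer more, and four stronger readings should be set aside.

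- *That the primary P value or interval is invalid.* No simulation showed type I error raised by leaving out the score. Nor was the unadjusted standard error visibly too large: in the third set of runs it averaged 0.342 and 0.340, against empirical standard deviations of 0.353 and 0.352. Adjustment raised it slightly, to 0.344 and 0.345. The power gain comes with a log odds ratio further from zero (0.98 rising to 1.03 at an odds ratio of 4 per step), not with a smaller standard error.
- *That the plan leaves two rival answers.* It ranks them: the adjusted models are sensitivity analyses. In the second and third sets of runs the two models fell on opposite sides of 0.05 in at most 1.4% of trials.
- *That the balanced demographics must also enter the primary model.* The protocol does not name them, so they cannot be prescribed or checked against the sensitivity list, and 39 to 47 events leave little room.
- *That leaving out stage of change is a mismatch.* Stage is not a stratification factor. Tailoring messages to it does not oblige the analysis to adjust for it.

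What the defence does not answer is why the stratification factor should stay out of the primary model when it is already collected and costs one term.

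**Conclusion.** The mismatch between stratified allocation and a treatment-only primary model is explicit, and worth correcting because the correction is nearly free. Its size is small: 0 to about 1.6 points of power, with slight conservatism at odds ratios of 3 to 4 per step (unadjusted type I error 0.039 to 0.044, adjusted 0.041 to 0.053). If dependence is weakly prognostic, the two models are practically the same.

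These figures rest on the planning rates of 4% and 10% and on the assumed strata, block size and prognostic strength. Balancing on demographics was not simulated, because the protocol does not describe it well enough. The conclusion concerns efficiency and consistency with the design; the planned test would not mislead.

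**What to change.** In Statistical analysis, define the primary model as logistic regression of CO-verified sustained abstinence at 6 months on treatment and baseline Fagerström score. Enter the score as the levels used for stratification or as one linear term, to keep the model small for 39 to 47 expected events. Report the unadjusted odds ratio alongside it. Keep living area, age, education and smoking frequency as additions in the sensitivity model; baseline stage of change may be added there but need not be. Settle the wording before outcomes are seen by arm.

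The cost is wording only: the score is already collected and the sample size is unchanged. The one trade-off is interpretation. The primary odds ratio becomes conditional on dependence, up to about 2.8 where the marginal value is 2.67, which is why the unadjusted figure should be shown beside it.

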### **Step 1 Development of mobile cessation intervention**

The design and development of this mobile cessation intervention followed three main stages.

The first stage was to develop the conceptual and theoretical framework, which was based on the interactive application of Transtheoretical Model (TTM) and Protection Motivation Theory (PMT).

TTM posits that health behavior change can be divided as six stages: pre-contemplation, contemplation, preparation, action, maintenance, and termination. It is a systematic theory of behavior change that states that health behavior is determined on a stage-to-stage basis. For any specific stage, there is intervention method to strengthen the behavior change occurrence and/or support to achieve next stage. The premise for using this theory is readiness for change. People in action, maintenance or termination stage will be normally excluded in high quality RCT design due to the homogeneity requirement.

PMT provides an important social cognitive account of protective behavior and has been extended to a more general theory of persuasive communication. There are studies applying the model to predict and evaluate protective behavior, particularly health behaviors. Applied to smoking cessation intervention, PMT theory will be used to adjust smoking behaviors' threat and coping appraisal. Behavioral intervention will be conducted from the perspective of those quitting attempt inducing factors to

enhance smokers' perception of the severity and susceptibility of smoking related diseases. The theories underlying intervention design are further described in **Table 1**.

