**Table 1. Conceptual and theoretical framework of Wechat application**

| Theory | Application                             | Description                                                                                                                                                                                                                                                                                                                                                                                                                                                                                                                                                                                         |
|---------------|------------------------------------------------|------------------------------------------------------------------------------------------------------------------------------------------------------------------------------------------------------------------------------------------------------------------------------------------------------------------------------------------------------------------------------------------------------------------------------------------------------------------------------------------------------------------------------------------------------------------------------------------------------------|
| TTM           | Actively identify smokers' stage               | Patients' willingness to quit will be assessed according to TTM. Smokers are divided as pre-contemplation, contemplation and preparation stage.                                                                                                                                                                                                                                                                                                                                                                                                                                                            |

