### **Table 2. Standard Protocol Item: Recommendation for Interventional Trials**

|                           |          | Follow-up (month) |   |   |   |
|---------------------------|----------|-------------------|---|---|---|
|                           | Baseline | 1                 | 2 | 3 | 6 |
| ENROLMENT                 |          |                   |   |   |   |
| Eligibility screen        | X        |                   |   |   |   |
| Informed consent          | X        |                   |   |   |   |
| Allocation                | X        |                   |   |   |   |
| INTERVENTIONS             |          |                   |   |   |   |
| Intervention group        |          | X                 | X | X |   |
| Control group             |          | X                 | X | X |   |
| ASSESSMENT                |          |                   |   |   |   |
| Smoking status            | X        | X                 | X | X | X |
| Nicotine dependence       | X        | X                 |   | X | X |
| Willingness to quit       | X        | X                 | X | X | X |
| Prolonged abstinence      |          | X                 | X | X | X |
| Health awareness          | X        | X                 | X | X | X |
| Self-efficacy             | X        | X                 | X | X | X |
| Utilization of the Wechat | X        | X                 |   | X | X |

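### The pre-specified covariate list for the adjusted abstinence models leaves out baseline stage of change, which is recorded for everyone and controlled by neither eligibility nor randomisation (minor)

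*Protocol*

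**What the plan says.** All references are to the protocol; no SAP is at hand.

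- **Statistical analysis.** The main logistic models contain treatment arm alone. For the sensitivity analyses, "each model will be further adjusted for baseline covariates: living area, age, education, smoking frequency and nicotine dependence at baseline". The covariates are named one by one and applied to every abstinence model.
- **Step 1.** The Transtheoretical Model (TTM) is described as holding that "health behavior is determined on a stage-to-stage basis".
- **Table 1.** A smoker's "willingness to quit will be assessed according to TTM", and "Smokers are divided as pre-contemplation, contemplation and preparation stage". Different strategies are then assigned to the different stages.
- **Table 2.** The row "Willingness to quit" is marked at baseline and at months 1, 2, 3 and 6, without distinction by arm.
- **Randomization.** Allocation uses "the score of the Fagerström Test for Nicotine Dependence as a stratified factor". In addition, "The WeChat system was also used to balance demographic characteristics". Stage is not mentioned.
- **Eligibility criteria.** None refers to stage or to intention to quit.
- **Primary and Secondary outcome.** Stage of change appears as a secondary outcome only.

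**The concern.** Every participant is given the same quit day, the 8th day after randomisation, and the primary outcome allows no cigarette after it. On the protocol's own model, a smoker in preparation is one step from action at that moment, while one in pre-contemplation is three steps away. Enrolment admits both. If the arms happen to differ in the mix of stages, part of the difference in abstinence may reflect that mix.

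Adjusted sensitivity analyses are there to show whether the result holds once baseline differences are allowed for. The fixed list returns to nicotine dependence, which is already a stratification factor, and to age and education, which the allocation system apparently also balances. It leaves out the readiness variable, which has no protection by design. If the descriptive baseline comparison then shows a difference in stage, any adjustment for it would be post hoc and open to challenge.

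**Working it through.** **1. The plan's own figure.** Inputs from the Sample size section: 4% versus 10%, two-sided 0.05, power 80%. With the unpooled normal formula, n = (1.960 + 0.842)² × (0.04 × 0.96 + 0.10 × 0.90) / 0.06² = 7.849 × 0.1284 / 0.0036 ≈ 280 per group, as stated. The total of 672 is 2 × 280 × 1.2, or 336 per arm. I use 336 per arm below because those who decline further data collection stay in the denominator as smokers.

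**2. Expected events.** 336 × 0.04 = 13.4 and 336 × 0.10 = 33.6, about 47 in all.

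**3. Assumptions, because the documents give no stage data.** Stages 40/35/25% (pre-contemplation, contemplation, preparation); abstinence odds rising 1.5-, 2- or 3-fold per stage. As a wider check, a two-level version with 20% to 50% in the most ready group and odds ratios of 2 to 5.

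**4. How large a chance imbalance is plausible.** The SD of the between-arm difference in a 25% share is √(2 × 0.25 × 0.75 / 336) = 3.34 points. A 5-point difference is 5 / 3.34 = 1.50 SD. The chance of 5 points or more in either direction is 0.134; against the intervention it is half of that, 0.067.

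**5. Average over randomisations** (simulated logistic models, 4,000 runs, likelihood-ratio test):

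| Odds ratio per stage | Power, arm only | Power, with stage |
|---|---|---|
| 1.5 | 0.878 | 0.877 |
| 2 | 0.872 | 0.878 |
| 3 | 0.886 | 0.896 |

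The two-level version gives the same picture, for example 0.866 against 0.876 at a 30% share and odds ratio 3. The average gain is about 0 to 1 point; a separate set of 3,000 runs put it at about 0 to 2.

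**6. Given a 5-point imbalance against the intervention** (5,000 runs):

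| Odds ratio per stage | Power, arm only | Power, with stage | Difference |
|---|---|---|---|
| 1.5 | 0.851 | 0.878 | 2.7 points |
| 2 | 0.839 | 0.885 | 4.6 points |
| 3 | 0.808 | 0.894 | 8.6 points |

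The separate 3,000 runs gave 0.844 and 0.873, 0.833 and 0.883, and 0.798 and 0.890, so differences of 2.9, 5.0 and 9.2 points. The median unadjusted odds ratio falls from about 2.7 to 2.6, 2.5 or 2.4. These figures fit the case where the displaced 5 points sit in pre-contemplation, two steps down; if they sit in contemplation the loss is smaller.

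**7. Size on the risk-difference scale.** In the two-level version the SD of the imbalance is 3.1 to 3.9 points. An imbalance of 1.96 SD (6.0 to 7.6 points) moves the crude abstinence difference, at a 4% rate, by about 0.2 points (odds ratio 2) to 0.5 points (odds ratio 5), against the planned 6 points.

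**8. Type I error.** With equal 4% rates, a 30% share and odds ratios of 2, 3 and 5 (3,000 runs each), rejection was 0.038 to 0.043 with arm only and 0.038 to 0.046 with stage. Leaving stage out does not inflate it.

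**The case against.** The strongest reply is that randomisation has already dealt with this. An arm-only comparison after equal, computerised allocation is valid, and its confidence interval already allows for chance imbalance in every covariate. The protocol nowhere undertakes to adjust for all prognostic variables, so choosing these five is a preference and contradicts nothing. It also plans a descriptive baseline comparison, where a difference in stage could be seen. Every input to the size of the effect is assumed. The sentence about stages describes a theory; it does not establish that baseline stage predicts verified 6-month abstinence among smokers who are all given a quit day.

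Most of this stands, and it rules out several stronger readings that a reader might infer:

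- *That the primary odds ratio is biased or its test invalid.* Neither follows; see step 8.
- *That the risk of harm is 13%.* That figure counts both directions. The loss arises in only one of them, at about 7%, and an equally likely imbalance would favour the intervention.
- *That extending the list lifts the trial's power from 81% to 89%.* The list serves sensitivity analyses only, and the primary model contains arm alone, so its power would not change.
- *That stage is shown to be the strongest prognostic factor.* The documents do not say so.
- *That secondary objective 2, "To identify whether certain patients are more likely to benefit from these interventions", lacks its stage interaction.* The choice of interaction can be left to an SAP.

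The reply does not remove the narrower point. The protocol itself fixes the list, so the omission is a stated choice and not a detail deferred to an SAP. A baseline table can reveal an imbalance, but it cannot show whether the result survives it.

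**Conclusion.** The point holds as a minor one. Stage is central to the trial's own rationale, scheduled at baseline, uncontrolled by eligibility or allocation, and absent from every abstinence model. As a result the adjusted analyses cannot answer whether the arms' readiness to quit explains the result.

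The expected cost is small: about 0 to 1 power point on average, and roughly 3 to 9 points in an unfavourable allocation with a chance of about 7%. Even there, unadjusted power stays close to the planned 80%. The direction of these results is secure. Their size rests on assumed stage shares and odds ratios, and on linking the Table 2 willingness-to-quit item to the three stages in Table 1, which Table 1 supports.

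**What to change.** In the Statistical analysis section, add baseline stage of change to the named covariates as one ordered term (pre-contemplation, contemplation, preparation), taken from the baseline willingness-to-quit assessment. One ordered term and two indicators gave the same simulated power, so the single term is enough.

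This improves the sensitivity models only. If the sponsor wants the precision for the primary result, the primary model must include the term as well, and this has to be decided before outcome data are seen.

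The cost is one line of text and no new data. The downside is one more parameter on about 47 events. Counting arm and each covariate as a single term, the adjusted model goes from 6 terms (47 / 6 = 7.8 events per term) to 7 (47 / 7 = 6.7), and to fewer if living area or education enters with several categories.
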